**Fig. 1 Fig1:**
[figure not shown]
Study procedures and characteristics of study visits

The primary objective is to evaluate, in sexually active women who present r-UTIs, the effects of a standardized cranberry extract containing 37 mg type-A linkage PACs per day, compared to a control dose of 2 mg PACs per day during a 6-month period on the incidence rate of newly symptomatic UTIs during a 6-month follow-up period. Secondary objectives are: (1) To evaluate the mean number of new symptomatic UTIs with pyuria as demonstrated by a positive leucocyte esterase test; (2) To detect the mean number of new symptomatic culture-confirmed UTIs; (3) To quantify urinary PACs metabolites in women who take a daily dose of 37 mg PACs per day compared to women who take a daily dose of 2 mg per day for 6 months; (4) To characterize women who present r-UTI based on known risk factors such as spermicidal contraception use, frequency of sexual relations, personal and familial history of UTI; (5) To describe the side effects of daily intake of cranberry extract containing 37 mg PACs compared to 2 mg PACs.

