#### Clinical follow-up

Each visit (0, 12 and 24 weeks) will include a short questionnaire documenting socio-demographic characteristics (*T* = 0 only), medication and natural health product intake, quality of life (SF-12) [23], risk factors for UTIs, and a validated food frequency questionnaire (FFQ) [24] modified for our study to specifically include foods containing PACs. Double data entry will be performed under the study coordinator supervision in order to promote data quality. Participants will be instructed to obtain a midstream urine sample according to standard methods suggested by the microbiological laboratory. A dipstick urinalysis using Chemstrip 9 (Roche Diagnostics USA) and a pregnancy test (ß-hCG) will be completed. Three 10 ml tubes will be placed in a − 80 °C freezer for urinary PAC metabolites measurements by ultra-high performance liquid chromatography coupled with mass spectrometry, and the urine sample for culture will be refrigerated and transported to the microbiology laboratory at the CHU de Quebec – Universite Laval within 24 h after collection.

During their participation, the women will be asked to contact the study coordinator if they present symptoms of UTI in order to schedule a visit at INAF to confirm the diagnosis by urinalysis and urine culture and to receive an appropriate antibiotic prescription based on their medical history and allergies. Women unable to present themselves at INAF will be prescribed antibiotics waiving a confirmation of their UTI. Women wishing to discontinue the consumption of capsules will be asked to present themselves at the 3 and 6-month visit in order to complete intention to treat analysis. The participants will be asked not to consume other products containing cranberry derivatives for the duration of the study and to consume their cranberry extracts 2–4 h preceding each visit. Participants will also be asked to limit intense physical activity for 24 h preceding each visit. After 24 weeks of participation, women will be provided with the option of prolonging their participation for an additional 24 weeks, with follow-up visits at 36 and 48 weeks. This data will provide information on seasonal variations in the incidence of UTI.

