#### Sample size and statistical analysis

Statistical analyses will be performed using SAS 9.2 (SAS Institute Inc., USA). All analyses will be based on the intention-to-treat principle before unmasking the treatment groups. The baseline characteristics of both groups will be compared using a Student’s t test for continuous variables and a generalized linear model for nominal variables. The Poisson regression model, which allows us to adjust for participants that were lost to follow up, will be used to compare the incidence of UTI during the 6-month follow up period as well as side effects of the treatment. Subgroup analyses will be performed in order to evaluate the impact of cranberry capsules in pre- and post-menopausal women as well as women with certain risk factors for complicated UTI such as pelvic floor disorders and diabetes.

Based on the literature [17], we estimate that 35% of patients in the control group will present at least one UTI during the 6-month follow-up period. In total, 126 women will need to be recruited in order to detect a clinically significant difference of 25% between the 2 groups (10% of women assigned to the experimental group will have at least 1 UTI with a power of 80%). Based on our past clinical trial experience [25], we estimate that 15% of randomized participants will be lost to follow up, therefore 148 women will need to be recruited in order to have at least 126 participants who will complete the 24-week intervention.

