### Compliance and side effects

The cranberry extract capsules will be distributed at each visit and participants will be asked to bring remaining capsules the next visit in order to count remaining capsules. The participants will fill out a daily journal to record compliance, transient UTI symptoms and any adverse effects related to capsule intake. A bi-monthly email reminder will be sent to encourage participation. Each participant will receive an email reminder in the week preceding each visit. Evaluation of side effects will take place at each visit and participants will be asked to document symptoms (nausea, dyspepsia, abdominal pain, bloating and headaches) in their daily journal. In the presence of severe side effects, participants will be allowed to discontinue the intervention and remain in the study in order to preserve the intention to treat analyses.

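### Comparing side effects only by intention-to-treat Poisson rate can dilute a 37 mg versus 2 mg difference, because weeks off capsules may count as time at risk

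*Protocol article*

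**What the plan says.** Under Sample size and statistical analysis, the protocol article sets one principle for everything: "All analyses will be based on the intention-to-treat principle before unmasking the treatment groups". No exception is made for side effects. The model is introduced as "The Poisson regression model, which allows us to adjust for participants that were lost to follow up", and the same sentence goes on to say that it "will be used to compare the incidence of UTI during the 6-month follow up period as well as side effects of the treatment". Loss to follow-up is the only adjustment of follow-up named.

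Two other sections decide who stays in follow-up. Clinical follow-up says: "Women wishing to discontinue the consumption of capsules will be asked to present themselves at the 3 and 6-month visit". Compliance and side effects says that, when side effects are severe, "participants will be allowed to discontinue the intervention and remain in the study in order to preserve the intention to treat analyses".

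The events of interest are tied to intake. The daily journal is to "record compliance, transient UTI symptoms and any adverse effects related to capsule intake", and secondary objective 5 is "To describe the side effects of daily intake of cranberry extract containing 37 mg PACs compared to 2 mg PACs".

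**The concern.** Intention to treat over full follow-up suits the UTI comparison, because a UTI can occur whether or not a woman still takes capsules. It fits less well for events defined by their relation to capsule intake. A woman who stops at week 4 and attends to week 24 is not lost to follow-up, so the one adjustment named does not reach her. If study time is the exposure, her 20 remaining weeks count as time at risk, although effects of intake are not expected in them.

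At stake is how the tolerability comparison reads. If one arm loses more women from capsules than the other, its side-effect rate is diluted more, and the ratio no longer describes the effects of daily intake that the objective names. The primary UTI result is not affected.

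**Working it through.** **Inputs.** From the documents: a 24-week intervention, 1:1 allocation, intention to treat for all analyses, and continued follow-up after stopping capsules. The documents give no side-effect rate, no rate of stopping capsules and no offset, so there is no planned figure to reproduce. The 15% in the sample-size paragraph is loss to follow-up, not stopping while staying in the study.

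**Assumptions.** A share s of an arm stops capsules at week w. The rate on capsules is r, set to 1 in the 2 mg arm and to 1.50 or 2.00 in the 37 mg arm. The rate off capsules is b, between 0 and the 2 mg on-capsule rate. Women who stop and women who continue share the same on-capsule rate.

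**Formula.** Rate over full follow-up = [r × ((1−s)×24 + s×w) + b × s × (24−w)] / 24.

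**Worked case.** 15% (37 mg) versus 5% (2 mg) stop at week 4, with b = 0.
- Mean weeks on capsules, 37 mg: 0.85×24 + 0.15×4 = 21.0.
- Mean weeks on capsules, 2 mg: 0.95×24 + 0.05×4 = 23.0.
- Multiplier on the rate ratio: 21.0/23.0 = 0.913.
- A ratio of 1.50 becomes 1.37, and 2.00 becomes 1.83.

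**Range.** Full-follow-up rate ratio when the on-capsule ratio is 1.50 / 2.00:

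| Stopping, 37 mg vs 2 mg | Week | b = 0 | b = 2 mg on-capsule rate |
|---|---|---|---|
| 5% vs 2% | 12 | 1.477 / 1.970 | 1.488 / 1.975 |
| 15% vs 5% | 4 | 1.370 / 1.826 | 1.438 / 1.875 |
| 20% vs 5% | 4 | 1.304 / 1.739 | 1.417 / 1.833 |
| 30% vs 10% | 4 | 1.227 / 1.636 | 1.375 / 1.750 |
| 10% vs 10% | 4 | 1.500 / 2.000 | 1.458 / 1.917 |

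The smallest shrinkage with unequal stopping is 1 − 1.488/1.50 = 0.8%. The largest is 1 − 1.227/1.50 = 18.2%. With equal stopping and b = 0 there is none. With equal stopping and background events counted off capsules, a small loss remains (1.50 to 1.458).

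**Direction.** With b = 0 the multiplier is weeks on capsules in the 37 mg arm divided by weeks on capsules in the 2 mg arm. If more women stopped on 2 mg (5% versus 15% at week 4), it would be 23.0/21.0 = 1.095, and 1.50 would become 1.64.

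**What capsule time cannot repair.** Suppose the women who stop are those with most symptoms. Take 30% (37 mg) and 10% (2 mg) as symptom-prone, with 3 symptom days a week against 0.1 in other women. Let 75% and 25% of the prone women stop at week 4, that is 22.5% and 2.5% of each arm, with no events afterwards.
- Nobody stops: (0.3×3 + 0.7×0.1)/(0.1×3 + 0.9×0.1) = 0.97/0.39 = 2.49.
- Events per woman, 37 mg: 0.225×4×3 + 0.075×24×3 + 0.7×24×0.1 = 9.78.
- Events per woman, 2 mg: 0.025×4×3 + 0.075×24×3 + 0.9×24×0.1 = 7.86.
- Weeks on capsules: 19.5 and 23.5.
- Ratio on capsule time: (9.78/19.5)/(7.86/23.5) = 1.50.
- Ratio on 24 weeks: 9.78/7.86 = 1.24.

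The denominator accounts for the step from 1.50 to 1.24, about one fifth of the whole fall. The rest arises because early stopping cuts short the counts of the worst-affected women, and an offset does not undo that.

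**The case against.** The strongest reply is that the denominator is inferred. The article states no offset for side effects, its reference to the 6-month period attaches to UTI incidence, and it does not say whether women, episodes or symptom days are counted. If women with any side effect were modelled without person-time, the problem would not arise. Such details may sit in an analysis plan that is not shown. This stands as a limit on certainty. It does not remove the point, because the article itself fixes the principle, the model and the retention rule, and a plan that follows them carries the issue forward. The primary end-point section, which has women with a UTI staying for the full period unless lost or off the intervention, also sits awkwardly with the two retention statements. That is a further reason to state whose time counts.

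Second, comparison by randomised arm over full follow-up is a legitimate treatment-policy estimate and keeps the protection of randomisation. This stands: the result should be kept, with an on-capsule comparison beside it.

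Third, the listed symptoms are non-specific and can occur off capsules, so weeks off capsules are not event-free by definition. This stands too. In the scenarios above, counting such events changes the amount of dilution but does not abolish it.

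A reader might infer that the plan hides a side-effect difference and so favours the 37 mg dose. The documents do not support that. Events before stopping are still counted, and true ratios of 1.50 and 2.00 stayed above 1 in every scenario tried. No passage shows that 37 mg is tolerated worse or that more women would stop on it.

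**Conclusion.** The point holds as a conditional one. Read as written, the plan's only stated between-arm comparison of side effects can attenuate a 37 mg versus 2 mg difference, by about 1% to 18% of the rate ratio over the assumed stopping rates. This rests on three things that the documents do not settle: that study time is the exposure, that stopping differs between arms or background symptoms are counted off capsules, and that more women stop on 37 mg. With equal stopping and no off-capsule events the effect is nil. The objective is secondary and worded as descriptive, so this is a worthwhile, inexpensive improvement and not a threat to the trial's main conclusion.

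**What to change.** Under Sample size and statistical analysis, limit sole reliance on intention to treat to the UTI endpoints. For side effects:

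1. State the event unit and the exposure time.
2. Add a Poisson comparison with time on capsules as the offset, reported beside the full-follow-up intention-to-treat rate.
3. Report by arm the proportion of women with at least one side effect and the proportion who stop capsules because of one.

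The cost is a few sentences and one derived variable, time on capsules. No new data are needed: the daily journal can supply the stopping date, and the capsule counts at visits can check it. The downside is that time on capsules is determined after randomisation and stopping may be informative. The on-capsule rate therefore corrects the dilution only in part, and it must be read together with the intention-to-treat rate and the stopping proportions.

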#### Study randomization

Concealed randomization will be generated using computer aided block randomization by blocks of 10. Eligible women will be assigned 1:1 to consume a cranberry extract either formulated in high PAC content capsules (2 capsules of 18.5 mg PAC per day) or low PAC content capsules (2 capsules of 1 mg PAC per day) for 6 months. The low PAC content cranberry capsule is comparable to the majority of cranberry extract products presently approved by Health Canada [21] . The standardized capsules will be manufactured and provided by Diana Foods and will be distributed in opaque packaging in order to conceal colour variations from the research team. The PAC content of each cranberry treatment will be validated at INAF according to the standardized BL-DMAC method, using A2 procyanidin dimer as standard for the quantification [22]. All clinical investigation, laboratory analysis, data collection and assessment will be blinded to the randomization allocation.

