## End points

### Incidence of UTI

The primary endpoint is the average number of symptomatic UTIs during the 6-month follow-up period. Individuals with acute urinary symptoms such as pollakiuria, urgency, burning, suprapubic pain, and hematuria will be assessed by study staff and will have to provide a urine sample for urinalysis. Women who present both symptom and pyuria criteria, defined as a positive leukocyte esterase dipstick result, will be diagnosed as having confirmed symptomatic UTI and prescribed appropriate antibiotic treatment. If the urine culture results are positive, the episode will be categorized as a culture-confirmed UTI. Women with symptomatic UTI during the study period will continue to take the cranberry capsules and remain in the study for the full 6 months unless they are lost to follow up or discontinue the intervention.

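### The 80% power is calculated for the proportion of women with at least one UTI, not for the Poisson comparison of UTI counts that is the primary analysis; at two-sided 5% it also does not match 126 women

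*Protocol article*

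**What the plan says.** All planning figures are in the protocol article, Sample size and statistical analysis. For the control arm, "we estimate that 35% of patients in the control group will present at least one UTI during the 6-month follow-up period". The total and the effect to be detected are given together: "In total, 126 women will need to be recruited in order to detect a clinically significant difference of 25% between the 2 groups", explained by the statement that "10% of women assigned to the experimental group will have at least 1 UTI with a power of 80" per cent. Then "we estimate that 15% of randomized participants will be lost to follow up", which raises the target to 148. Under Study randomization the allocation is 1:1, so 126 means 63 women per arm.

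The outcome that decides the trial is defined elsewhere. Under Incidence of UTI: "The primary endpoint is the average number of symptomatic UTIs during the 6-month follow-up period". The Abstract also names a mean number of UTIs as primary outcome, and the primary objective speaks of an incidence rate. The analysis, described in the same section as the sample size, is a Poisson regression of UTI incidence over 6 months.

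The article states no alpha, sidedness, or test for the sample size. It gives no control mean, rate ratio or dispersion for the count.

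**The concern.** The power statement concerns a yes/no outcome (any UTI in 6 months), while the primary analysis uses every episode. The two proportions alone do not fix power for a count. That also depends on the mean number of episodes per woman and on how much this number varies between women. Repeat episodes are to be expected: entry requires recurrent UTI, and women stay on capsules and in follow-up after an episode.

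A second problem is that the stated pairing of 126 women with 80% power does not follow from 35% versus 10% at the conventional significance level.

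At stake is how the result is read. A null result on the count would be judged against a power figure for another outcome, and the reader cannot tell what rate ratio the trial could detect.

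**Working it through.** **Inputs from the article:** p1 = 0.35, p2 = 0.10, difference d = 0.25, mean proportion 0.225, power 80%, 1:1 allocation, 126 completers (n = 63 per arm), 15% loss. **Assumed, because not stated:** two-sided alpha 0.05, so z = 1.960 and 0.842.

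**1. The plan's own figure, 126 at 80% power**

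Pooled formula: n per arm = [z(alpha)·√(2·0.225·0.775) + z(power)·√(0.35·0.65 + 0.10·0.90)]² / 0.25²

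| Method, two-sided 5%, 80% power | Per arm | Total |
|---|---|---|
| Unpooled variance | 39.9 → 40 | 80 |
| Arcsine | 41 | 82 |
| Pooled | 42.6 → 43 | 86 |
| Fisher exact (power 0.798 at 48, 0.809 at 49) | 49 | 98 |
| Pooled, continuity-corrected | 50.3 → 51 | 102 |

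None gives 126. One-sided 5% moves further away (68, or 84 corrected). Two-sided 5% at 90% power gives 114, or 130 corrected.

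A stricter alpha at 80% power does come close. Two-sided 1% without correction gives 63.7 → 64 per arm, 128 in total, with 79.4% power at 63 per arm. One-sided 1% with correction gives 62.4 → 63 per arm, exactly 126.

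**2. Power of 63 per arm for 35% versus 10%, two-sided 5%**

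- Standard error under no difference: √(2·0.225·0.775/63) = 0.0744. Under the planned difference: √[(0.2275 + 0.09)/63] = 0.0710.
- Pooled: Φ[(0.25 − 1.960·0.0744)/0.0710] = Φ(1.467) = 92.9%.
- Fisher exact, by enumeration: 90.6%.
- Continuity-corrected (0.25 reduced by 1/63): 89.3%.

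**3. Loss to follow-up**

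126/0.85 = 148.2, and 148 × 0.85 = 125.8. This step is acceptable.

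**4. The primary analysis (count)**

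Assumption: episodes are Poisson, so a mean m gives a proportion with at least one UTI of 1 − exp(−m).

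- Control mean −ln(0.65) = 0.431; experimental mean −ln(0.90) = 0.105.
- Rate ratio 0.105/0.431 = 0.245; its log is −1.408.
- Variance of the log rate ratio without overdispersion: (1/0.431 + 1/0.105)/63 = 0.1875.
- Overdispersion enters either as a multiplier of this variance, or as an added 2k/n (negative binomial form with dispersion k).
- Power = Φ(1.408/SE − 1.960).

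| Variance assumption | Variance | Power at 63 per arm |
|---|---|---|
| No overdispersion | 0.1875 | 90% |
| k = 1 (adds 2/63 = 0.0317) | 0.2192 | 85% |
| Multiplier 1.35 | 0.2531 | 80% |
| Multiplier 1.5 | 0.2813 | 76% |
| Multiplier 2.0 | 0.3750 | 63% |

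**5. Detectable rate ratio RR at 80% power, 63 per arm**

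Solve −ln RR = (1.960 + 0.842)·√[(1 + 1/RR)/(63·mean) + 2k/63]:

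| Control mean (assumed) | k = 0 | k = 1 |
|---|---|---|
| 0.43 | 0.35 | 0.29 |
| 1.0 | 0.55 | 0.45 |

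**The case against.** **The 80% is simply wrong.** A reader might infer a plain arithmetic error. The document does not support that, because alpha and test are unstated and a 1% level recovers 126 or nearly so. Nothing in the article points to a 1% test, but the figure cannot be called impossible. What stands is conditional: at two-sided 5%, 126 and 80% do not belong together.

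**The trial is underpowered.** This is the other tempting inference, and it is not shown either. On the binary scale 126 is more than needed. On the count scale, the planned rate ratio of 0.245 is more extreme than every detectable ratio in the last table, and it keeps 85 to 90% power at control mean 0.43 with k of 0 or 1. Power drops below 80% only beyond a variance inflation of about 1.35, and no figure in the article says whether that will occur.

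**The article condenses a fuller protocol.** Alpha, formula and count-scale power may be stated there, so their absence is not the point. The point is what the article does state: a power figure tied to one outcome and a primary analysis of another, in the same section. A fuller document could explain 126, but it would not make the printed 80% apply to the Poisson comparison.

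**Conclusion.** The point holds in conditional form and should be fixed; it does not undermine the design.

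- **Endpoint mismatch, the main part.** The stated 80% is not a property of the primary analysis. This follows from the text alone. Its size depends on assumptions: with the Poisson conversion of 35% and 10%, power runs from about 90% (no overdispersion) to 63% (variance doubled).
- **Binary arithmetic, the lesser part.** At two-sided 5%, 80% power needs about 86 to 102 women, and 126 gives about 89 to 93%. The discrepancy is on the safe side. It rests on the assumed alpha.

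The control mean of 1.0 and all dispersion values are illustrations, not document figures.

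**What to change.** Keep the enrolment target and the inflation to 148. In Sample size and statistical analysis:

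1. Say that 126 evaluable women give about 89 to 93% power for 35% versus 10% at two-sided 5%, naming the test. Alternatively, state the alpha and formula that give 126 at 80%.
2. Say that this figure concerns the proportion with at least one UTI. Then add the power or detectable rate ratio for the Poisson primary analysis over a stated range of control mean and dispersion, for example the four ratios in the last table above.
3. Narrow that range with the pooled, blinded event rate and variance before unmasking. Under Trial status, recruitment is complete and follow-up is still running, so this was still possible when the article was written.

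The cost is a reworded paragraph and about an hour of calculation. No extra patients are needed, and endpoint, model and allocation stay as they are.

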## End points

### Incidence of UTI

The primary endpoint is the average number of symptomatic UTIs during the 6-month follow-up period. Individuals with acute urinary symptoms such as pollakiuria, urgency, burning, suprapubic pain, and hematuria will be assessed by study staff and will have to provide a urine sample for urinalysis. Women who present both symptom and pyuria criteria, defined as a positive leukocyte esterase dipstick result, will be diagnosed as having confirmed symptomatic UTI and prescribed appropriate antibiotic treatment. If the urine culture results are positive, the episode will be categorized as a culture-confirmed UTI. Women with symptomatic UTI during the study period will continue to take the cranberry capsules and remain in the study for the full 6 months unless they are lost to follow up or discontinue the intervention.

